---

## **Statement of Compliance**

The study will be carried out in accordance with Good Clinical Practice as required by the Edinburgh revision (October 2000) of the Declaration of Helsinki as far as adopted by the concerned regulatory authorities, as well as International Conference on Harmonisation, Good Clinical Practice E6, and the National Institutes of Health (NIH) Clinical Terms of Award. The study will also be conducted in accordance with the applicable national and local requirements regarding ethical committee review, informed consent, and other statutes or regulations regarding the protection of the rights and welfare of human subjects participating in biomedical research.

---

### **List of Abbreviations**

|        |                                                                                       |
|--------|---------------------------------------------------------------------------------------|
| Ab     | Antibody                                                                              |
| ADE    | Ab dependent enhancement                                                              |
| CIDVR  | Center for Infectious Disease and Vaccine Research, UMMS                              |
| CRF    | Case Report Form                                                                      |
| DF     | Dengue fever                                                                          |
| DHF    | Dengue hemorrhagic fever                                                              |
| DMID   | Division of Microbiology and Infectious Diseases, NIAID, NIH,
DHHS                 |
| DV     | Dengue virus                                                                          |
| EIA    | Enzyme linked immunosorbent assay                                                     |
| EPI    | Extended Programme in Immunization                                                    |
| HAI    | Hemagglutination inhibition                                                           |
| N      | Number (typically refers to subjects)                                                 |
| NIAID  | National Institute of Allergy and Infectious Diseases, NIH, DHHS                      |
| NIH    | National Institutes of Health                                                         |
| PBMC   | Peripheral blood mononuclear cells                                                    |
| QA     | Quality assurance                                                                     |
| RITM   | Research Institute of Tropical Medicine, Department of Health,
Manila, Philippines |
| RT-PCR | Reverse transcriptase-polymerase chain reaction                                       |
| UMMS   | University of Massachusetts Medical School                                            |
| WHO    | World Health Organization                                                             |

## **Protocol Summary**

**Title:** A Prospective Study of Dengue Virus Infections during Infancy to Define Correlates of Protective Immunity.

**Population:** Healthy infants between the ages of 6 weeks-16 months and their mothers in the San Pablo Health District, Laguna, Philippines.

**Number of subjects to be enrolled:** 10,000 mother-infant pairs.

**Number of Sites:** 7 sites, San Pablo Health District, Laguna, Philippines

**Study Duration:** 4 years

**Subject Duration:** 50-58 weeks

### **Objectives:**

#### Primary:

- Define the levels of serotype-specific neutralizing antibody (Ab) associated with protective immunity against symptomatic dengue.

#### Secondary:

- Delineate specific viral, infant, and maternal factors contributing to the development of dengue hemorrhagic fever (DHF) among infants experiencing primary dengue virus (DV) infections.
- Strengthen the capacity for diagnosis and research on dengue in the Philippines.

### **Schematic of Study Design:**

(see page vi)

[figure not shown]

Additional surveillance for non-hospitalized dengue/acute febrile illness for 5 months between June-October of a calendar year. Acute/convalescent blood draws (3 ml each)†. Convalescent blood draws taken 10-14 days after acute illness blood draw.† Participating infants cannot have > 2 paired (acute and convalescent) surveillance blood samples taken while in the study.

**Optional:**

## 2 BACKGROUND INFORMATION AND SCIENTIFIC RATIONALE

### 2.1 Background Information

In dengue endemic countries such as the Philippines, there is an urgent need for a dengue vaccine; however, there is also major concern that widespread use of a vaccine may increase the risk for dengue hemorrhagic fever (DHF). Thus, it is critical that reproducible correlates of protective immunity be identified. The goal of this proposal is to identify correlates of protective immunity against dengue in a prospective study of DV infections during infancy. Unlike older children, infants manifest symptomatic dengue (including DHF) following primary DV infections that are modified by pre existing, maternally-acquired, humoral immunity. The unique immunological conditions of infancy provide the most unadulterated setting to define protective immune correlates.

**We hypothesize that specific levels of maternally-acquired neutralizing antibodies (Abs) are associated with protection against symptomatic dengue during infancy, and protective Ab levels differ among the DV serotypes. When maternally-derived anti-DV Abs fall below protective levels, we hypothesize that virus replication following a primary DV infection can stimulate a convergence of host pathogenic factors unique to infancy and lead to DHF.**

Dengue is an emerging arboviral disease caused by infection with one of the dengue viruses (DVs), a group of four antigenically related mosquito-borne flaviviruses. The DVs are widespread throughout the tropics and produce significant morbidity and mortality in at least 1/2 million persons/year [1]. The World Health Organization (WHO) has categorized dengue as a high priority emerging viral disease, as over 1 billion people in the world are at risk for DHF. Infection with any 1 of the 4 DV serotypes (DV-1, DV-2, DV-3, DV-4) can produce a spectrum of illness. The manifestations of a DV infection range from asymptomatic or mild febrile illness, to the more symptomatic dengue fever (DF), to the most severe and potentially life-threatening illness, DHF. The cardinal feature of DHF, as in other viral hemorrhagic fevers, is rapid and severe vascular dysregulation. The vascular dysfunction contributes to thrombocytopenia, a coagulopathy, and, most importantly, a transient increase in vascular permeability. The circulating blood volume is reduced, hemoconcentration occurs, and, in severe cases, hypovolemic shock develops [2, 3]. Fluid resuscitation and intensive care can be life saving, but specific treatments are not available and often access to appropriate care is limited. So far, the main preventive strategy in dengue endemic countries is mosquito control of the primary DV vector, *Aedes aegypti*. Despite some success in a few countries, widespread mosquito control efforts have been difficult to sustain. Development of a vaccine is seen as the only practical strategy for effective prevention and long-term control of dengue disease. The vaccines under development that are likely to be considered for use in dengue endemic countries are live-attenuated or chimeric viruses combined in a tetravalent formulation. Beyond the problems of interference in multivalent viral vaccines, there are additional and somewhat unique

immunological issues in dengue that will pose challenges to mass, public health, vaccination campaigns against dengue.

A primary infection with one DV serotype typically produces long-term protective immunity against the homologous serotype. After a short period of cross-protection, individuals who have recovered from a primary DV infection are fully susceptible to infection and disease by heterologous serotypes (secondary infection) [4, 5]. In fact, the relative risk of developing DHF is enhanced 5 to 500-fold following sequential, heterotypic DV infections [6-8]. For dengue vaccines, even tetravalent ones, the key unanswered question remains what are the vaccine-induced immune responses that will recapitulate natural infection induced protective immunity and avoid enhancement of disease severity? The potential pitfalls of a dengue vaccination campaign are that ineffective or short-lived vaccine induced immune responses would not only fail to protect against disease, but could enhance disease severity in vaccinated individuals. Given these consequences, it is imperative that clear and reproducible correlates of protective immunity are well defined before large scale dengue vaccine clinical trials and public health vaccination programs begin.

The majority of clinical studies on dengue have focused on secondary DV infections and identifying risk factors for development of DHF. There have been 5 community-based, prospective, studies of dengue reported in the literature [6, 9-12]. All have consistently found that pre existing anti DV immunity, generally reflecting prior infection with heterologous DV serotypes, is associated with development of DHF. In a recent paper [13], we focused on examining correlates of protective anti DV immunity in a prospective cohort study of schoolchildren in Thailand. We found that the presence of pre existing neutralizing Abs directed against the infecting DV serotype (either a prototype strain or the infecting virus isolate) was not a good correlate of disease protection for secondary D1V, D2V, and D3V infections. So far, the protective capability of dengue vaccine candidates has been inferred by their ability to induce detectable neutralizing Ab responses. Our data suggest that the presence of neutralizing Abs is unlikely to be an adequate immune correlate for selecting, testing, and using dengue vaccines. Vaccines inducing and sustaining higher levels of neutralizing Abs would be considered better than those inducing lower Ab levels. What levels of neutralizing Ab to a given DV serotype can be considered “protective” or “adequate” is the primary unanswered question that this proposal aims to address.

For many different viruses, animal models, and challenge routes, passive Ab transfer experiments have consistently shown a good correlation between in vivo protection and the Ab neutralizing activity measured in vitro [14]. Even though the correlation does not necessarily imply that the mechanism of neutralization in vitro is the only, or even predominant, mechanism of protective activity in vivo. As there is no animal model for DHF, studies of dengue in infants born to DV immune mothers are the best approximations of passive immunization experiments. A careful examination of dengue in infants is the most unadulterated way to identify protective immune correlates in a clinical study, and cannot be replicated in studies of secondary DV infections. There have been very few studies of infant dengue to date, and none focusing on correlates of protective immunity.

Insight into protective immunity in dengue can also be gained by studying the converse process, immune enhancement of disease severity. DHF among infants (age < 12 months) was

first reported in 1970 [8]. In contrast to childhood DHF, DHF among infants occurs almost exclusively in the setting of a primary DV infection. Epidemiological data from four Southeast Asian countries have shown a similar age distribution pattern for hospitalized infant DHF [15]. There are few cases at < 3 months and the largest number of cases is typically between 6-9 months. The number of infant DHF cases then decreases variably over the remainder of the first year of life. A unifying explanation of childhood DHF following secondary DV infection and infant DHF following primary DV infection has been the presence of circulating anti-DV Abs, either actively acquired (from earlier primary infection) or passively acquired (from maternal-fetal transfer). When DV serotype cross reactive Abs are at sub neutralizing concentrations, it is postulated that they facilitate DV entry into Fc-receptor-bearing cells, thereby increasing the virus burden and severity of disease. This has been termed Ab dependent enhancement (ADE) of infection. ADE of DV infection in monocytes and other Fc receptor bearing cells has been demonstrated in some in vitro and ex vivo studies [16, 17]. ADE of DV infections has been considered the only risk factor that infants have for developing DHF, and therefore the only unifying explanation for immune enhancement of dengue disease severity. However, there has been only one small infant study using ex vivo blood samples in an attempt to explain the epidemiological findings [18]. A careful look at the limited data available on infants to date reveals many unanswered questions.

We feel that a carefully designed, comprehensive, prospective study of DV infections over the first 16 months of life will successfully avoid some of the pitfalls of previous studies, and narrow the gaps in knowledge regarding immune correlates of protection against symptomatic dengue and delineation of important factors in the pathogenesis of DHF. To that end, a collaborative and international consortium has been formed to advance dengue research in the Philippines. The research will generate vital data for the effective testing of dengue vaccines and future public health vaccination campaigns throughout the region.

## 2.2 Scientific Rationale

Our long-term aim is the prevention of DHF and hospitalized dengue in children with a safe and effective vaccine. This collaborative study will provide immediately relevant, sound, scientific data useful for selecting and testing dengue vaccine candidates in Phase III clinical trials, as well as for future implementation of dengue vaccine campaigns. A prospective study of primary DV infections during infancy provides a unique opportunity to identify correlates of immune protection or immune enhancement not provided by studies of secondary DV infections. While some vaccines have been developed without identifying correlates of immune protection, the potential harm caused by ineffective or incomplete immunity to DVs makes a better understanding of immunity in dengue critical for the advancement of vaccination campaigns. Results from this study are likely to have a significant impact on future dengue vaccination testing and administration policies in the Philippines and other Southeast Asian countries.

There is no animal model for DHF or DF. As such, prospective human studies of natural DV infections are critical for advancing dengue vaccine development and usage.

## **2.3 Potential Risks and Benefits**

### **2.3.1 Potential Risks**

#### **a) Phlebotomy –**

- Immediate risks- can infrequently cause temporary bruising, erythema, pain, infection, or bleeding.
- Long range risks- none.
- Rationale- There are no direct health benefits from the collection of blood samples to the subjects. The minimal risks of phlebotomy are reasonable and necessary to successfully address the study objectives, namely identify immunological correlates of protection to dengue.
- To diminish the risk of phlebotomy, only adequately trained study personnel will draw blood. Blood volumes taken from the study subjects fall within the Office of Human Research Protections guidelines for minimal risk studies [19]. Alternative procedures are not feasible.

### **2.3.2 Known Potential Benefits**

#### **i) Participation in study may improve outcome in DV infections.**

The morbidity and mortality from DHF is often from a delay in seeking medical care. Parents in the study will be educated and encouraged to bring their infants to medical attention for febrile illnesses. Early medical evaluation of dengue can offset the severe consequences of the disease.

#### **ii) Study will provide rapid dengue diagnostic testing for acute febrile illnesses.**

In infants with an acute febrile illness identified either during hospitalization or during outpatient surveillance during the peak DV transmission season, an acute illness blood sample will be obtained and tested using a DV IgM enzyme-linked immunosorbent assay (EIA) and DV reverse transcriptase-polymerase chain reaction (RT-PCR). The results of the assays and an interpretation of their significance will be reported to the parent/guardian and healthcare provider of the ill child within 2-3 days. These diagnostic tests will be performed at no cost to the subject. If the child requires additional medical attention, this information will be provided to the appropriate healthcare provider to assist in the clinical management.

#### **iii) Compensation at study visits-**

a) Study Visit 1- study will pay for transportation to and from City Health Office and provide an infant digital thermometer and multivitamin with iron for mothers.

b) Study Visit 2- study will pay for transportation to and from City Health Office and provide a food tray with utensils, sipping cup, and educational information on dengue.

c) Study Visit 3 (if selected)- study will pay for transportation to and from City Health Office and parents will receive a framed photograph of their child.

d) Study exit (age 16 months)- all children will receive a toy, not valued greater than \$1 USD.

### 3 OBJECTIVES

#### Primary Objective

- The first aim of this project is to define levels of serotype-specific neutralizing Abs associated with protective immunity against symptomatic dengue. Neutralizing Ab titers in blood samples collected from Filipino infants before DV infection, and predicted neutralizing Ab titers at the time of illness, will be correlated with disease severity rankings and peak viremia levels. Neutralizing Ab titers at which infants developed symptomatic dengue will be determined.

#### Secondary Objectives

- The second aim is to delineate risk factors contributing to the pathogenesis of DHF in infants. From pre-illness blood samples, the association of Ab neutralizing capacity or enhancement of infection with DHF will be measured while controlling for other potential covariates. The covariates will include measures representing viral load and infant host immune responses.
- The third aim is to strengthen the capacity for diagnosis and research on dengue in the Philippines. A collaborative and international consortium has been formed to advance dengue research in the Philippines. The research will generate vital data for the effective testing of dengue vaccines and future public health vaccination campaigns throughout the region.

## 4 STUDY DESIGN

This is a prospective natural history study to define the levels of maternally-acquired neutralizing Ab and other correlates of immunity that may be protective against the development of dengue hemorrhagic fever in infants. Approximately 10,000 mother-infant pairs will be enrolled to achieve a continuous study cohort of approximately 4,000 children less than 16 months of age. Children leave the study when they reach 16 months of age and are replaced by new participants at 6-14 weeks of age.

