## 5 Study Population

### 5.1 Selection of the Study Population

Up to 10,000 healthy mother-infant pairs will be enrolled over a 4 year period. Infants will be between 6-14 weeks of age at enrollment and will be followed until they are 16 months of age. The goal is to maintain a continuous cohort of approximately 4,000 infants at any time, replacing those who go off study at 16 months of age with new subjects. Thus, study subjects will be infants, male or female, between the ages of 6 weeks to 16 months, of any race or ethnicity. The infants' mothers will also be included as study subjects (no age restriction). Infants with congenital medical conditions or born to HIV seropositive mothers (obtained by history) will be excluded so that these factors do not become confounding variables in the study. Pregnancy HIV testing will not be required. The study population will be drawn from infants born to mothers residing in the San Pablo City Health District, Laguna, Philippines. Study subjects will be recruited and enrolled in outpatient public health clinic settings.

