#### Time of participation

The expected total duration of an infants' participation is between 50-58 weeks, from the age of 6-14 weeks to 16 months. The total duration of the mothers' participation is one study visit upon study entry.

| Study visit             | Time required                      |
|-------------------------|------------------------------------|
| Study Visit #1 (infant) | 1.5 hours                          |
| Study Visit #1 (mother) | 1.5 hours (concurrent with infant) |
| Study Visit #2 (infant) | 1 hour                             |
| Study Visit #3 (infant) | 1 hour                             |

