### 7.2 Sample Size Considerations

- Dengue surveillance in San Pablo City over the past 4 years has demonstrated annual incidence rates of infant hospitalized dengue between 0.05-0.25%. The

population of infants between 0-16 months of age in San Pablo City is approximately 16,000-20,000. A study cohort continuously maintained at 4,000 subjects in this age range will capture infant hospitalized dengue rates of 0.1-0.2% with 90% confidence (EpiInfo, [www.cdc.gov/epiinfo](http://www.cdc.gov/epiinfo)).

- To identify subjects with mild/asymptomatic dengue, we will measure asymptomatic seroconversion in a subset of 250 subjects/year. We anticipate a 1-3% yearly incidence of mild/asymptomatic dengue [12]. A sample of 250 subjects will capture a mild/asymptomatic dengue incidence rate of 1-3% with 90-95% confidence (EpiInfo, [www.cdc.gov/epiinfo](http://www.cdc.gov/epiinfo)).
- Based on these sample sizes and assumptions, we anticipate capturing the following number of subjects over a 4-year period:

| Hosp DHF | Hosp DF | Non-hosp DF | Mild/asymptomatic seroconversion
(from random sample of $n=250/\text{year}$ ) |
|----------|---------|-------------|----------------------------------------------------------------------------------|
| 11       | 11      | 44          | 32                                                                               |

At the end of the study period, we expect to have nearly  $n=100$  infants with DV infections, and a much larger pool without evidence of DV infections to select matched controls ( $n=200$  or  $300$ ). Data analysis with these anticipated numbers is detailed in section 7.4.

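### Up to 10,000 enrolments at 50–58 weeks each supply about 65% (71% in calendar months) of the infant-years that a cohort of 4,000 needs over 4 years, so the enrolment and cohort figures cannot both hold

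*Protocol*

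**What the plan says.** Three figures define the accrual plan.

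- **Enrolment.** Section 5.1: "Up to 10,000 healthy mother-infant pairs will be enrolled over a 4 year period". Section 4 ties that total to the cohort: "Approximately 10,000 mother-infant pairs will be enrolled to achieve a continuous study cohort of approximately 4,000 children less than 16 months of age".
- **Cohort.** Section 5.1: "The goal is to maintain a continuous cohort of approximately 4,000 infants at any time". Section 7.3 has leavers at 16 months replaced on a rolling basis after start-up.
- **Time on study.** Section 6.1: "The expected total duration of an infants' participation is between 50-58 weeks, from the age of 6-14 weeks to 16 months". The Protocol Summary repeats 50–58 weeks and gives "Study Duration: 4 years".

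Section 7.2 assumes that the cohort of 4,000 is held throughout and plans on hospitalised dengue rates of 0.1–0.2% with 90% confidence. For mild or asymptomatic infection it takes a subset of 250 infants per year: "We anticipate a 1-3% yearly incidence of mild/asymptomatic dengue". It then states: "Based on these sample sizes and assumptions, we anticipate capturing the following number of subjects over a 4-year period". The table lists 11 hospitalised DHF, 11 hospitalised DF, 44 non-hospitalised DF and 32 seroconversions, a total of 98.

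**The concern.** If each infant stays for roughly one year, a cohort of 4,000 turns over about once a year. Four years would then need well over 10,000 infants. The protocol nevertheless offers 10,000 as both the ceiling on enrolment and the number that delivers the cohort.

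The case table is the only sample-size justification in the protocol. The DHF cases are the events in the stepwise logistic model for the second objective. The symptomatic cases feed the serotype-specific severity models and the estimated titres at which 25%, 50% and 75% of subjects develop symptomatic infection (section 7.4). There is also a practical conflict: a site that keeps replacing leavers as section 7.3 requires would reach the section 5.1 ceiling before the 4 years are over.

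**Working it through.** **Inputs.** Enrolment 10,000 (sections 4 and 5.1); cohort 4,000 (sections 4, 5.1, 7.2 and 7.3); follow-up 50–58 weeks, midpoint 54 (Protocol Summary, section 6.1); duration 4 years; table counts 11, 11, 44 and 32 (section 7.2). No dropout rate is given, so I assume zero, which favours the plan. One year = 365.25/7 = 52.18 weeks.

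**The plan's own figures first.** A cohort of 4,000 for 4 years is 16,000 infant-years. The 22 hospitalised cases are 22/16,000 = 0.1375%, inside the planned 0.1–0.2% (16–32 cases). The table is therefore consistent with 16,000 infant-years. The cohort size also reproduces if one assumes the single-proportion formula with p = 0.2%, half-width 0.1%, 90% confidence and a finite population of 16,000, which gives n = 4,038. With a population of 20,000 it gives 4,252.

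**Participation time.** Sixteen calendar months are 16 × 365.25/12/7 = 69.57 weeks. Entry at 6–14 weeks leaves 55.6–63.6 weeks (59.6 from age 10 weeks). The stated 50–58 weeks appears only with 4-week months: 64 − 14 = 50 and 64 − 6 = 58.

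**Infant-years from 10,000 enrolments** = 10,000 × weeks/52.18:

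| Follow-up per infant | Infant-years | Share of 16,000 | Mean cohort over 4 years | Years at 4,000 |
|---|---|---|---|---|
| 50 weeks | 9,582 | 60% | 2,396 | 2.4 |
| 54 weeks | 10,349 | 65% | 2,587 | 2.6 |
| 58 weeks | 11,116 | 69% | 2,779 | 2.8 |
| 55.6 weeks (calendar) | 10,650 | 67% | 2,663 | 2.7 |
| 59.6 weeks (calendar) | 11,417 | 71% | 2,854 | 2.9 |
| 63.6 weeks (calendar) | 12,183 | 76% | 3,046 | 3.0 |

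No row reaches 16,000. Turned round, 16,000 infant-years need 16,000/(54/52.18) = 15,460 enrolments, or 14,014 at 59.6 weeks, before dropout.

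**Expected symptomatic cases at the implied rate.** Scaling the table by the two midpoints (10,349/16,000 = 0.647 and 11,417/16,000 = 0.714):

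- DHF: 11 → 7.1 to 7.8
- Hospitalised DF: 11 → 7.1 to 7.8
- Non-hospitalised DF: 44 → 28.5 to 31.4
- All symptomatic: 66 → 42.7 to 47.1

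**Seroconversions.** 250 × 4 × 1–3% = 10–30. The 32 equals 250 × 3% = 7.5, rounded up to 8 per year, times 4. The subset is fixed at 250 per year, so this count does not scale with the cohort.

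**Top of the protocol's ranges.** At 0.2% and 11,417 infant-years there are 22.8 hospitalised cases. The table's 2:1 ratio of non-hospitalised to hospitalised cases adds 45.7. With 3% seroconversion (30), the total is 98.5. At 10,349 infant-years the same steps give 20.7 + 41.4 + 30 = 92.1.

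**The case against.** The strongest defence is that the case counts need not fall. The 0.1375% rate is back-calculated and the protocol does not state it. Section 7.2 plans on 0.1–0.2% and reports 0.05–0.25% from past surveillance, and that fivefold spread outweighs a factor of 65–71%. This stands: the lower counts are conditional on the rate. It does not rescue the enrolment figure, which fails whatever the rate.

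The protocol also speaks of a goal and of approximate numbers, and maintenance begins only after start-up. Approximate wording does not cover a gap of 24–40%. Dropout, build-up from zero, entry at up to 24 weeks of age in the first five months, and late enrolees cut off at study end would all reduce the infant-years further.

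Four stronger readings are tempting but not supported:

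- **The total falls from 98 to 53–77.** That range joins two follow-up lengths (53–73 at 10,349 infant-years, 57–77 at 11,417). Its low end also replaces the table's seroconversion rate of about 3% with 1%. With the 32 left alone, the change in infant-years gives 42.7 + 32 = 75 to 47.1 + 32 = 79.
- **The 32 contradicts the 1–3% range.** It is two infants above 30 because of yearly rounding. The fair remark is only that the table uses the top of its range.
- **A cohort of 4,000 is unreachable.** It can be reached; 10,000 enrolments cannot hold it for 4 years.
- **The 90% confidence drops to 79%.** That figure needs a half-width that the protocol does not give.

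**Conclusion.** The point holds as a contradiction between enrolment, cohort size and study length. With no dropout, 10,000 enrolments give 60–69% of the required infant-years at the stated participation time, and at most 76% if every infant enters at 6 weeks and stays to 16 calendar months. They support a mean cohort of about 2,400–3,050.

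The effect on yield is expected but not certain. At the table's implied 0.1375%, plan on about 7–8 DHF, 7–8 hospitalised DF and 28–31 non-hospitalised DF. Reaching about 98 infections requires hospitalised dengue at 0.2%, seroconversion at 3%, the table's 2:1 ratio, calendar-month follow-up and no dropout, all together.

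The 50–58 week figure is a separate and smaller discrepancy. Correcting it narrows the gap but does not close it.

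**What to change.** Reconcile the Protocol Summary and sections 4, 5.1, 6.1, 7.2 and 7.3:

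1. Keep 10,000 enrolments and restate the sustainable mean cohort (about 2,400–3,050 before dropout), or state for how long 4,000 will be held.
2. Correct participation to about 56–64 weeks.
3. Restate the section 7.2 table as ranges with the assumed rates shown: about 7–8 DHF, 7–8 hospitalised DF and 28–31 non-hospitalised DF at 0.1375%, and 10–30 seroconversions at 1–3%.
4. Recompute the 90% confidence statement for the restated cohort and state its half-width. As an illustration only, with p = 0.2%, half-width 0.1% and a population of 16,000, a cohort of 2,590 gives about 79%.

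These changes cost wording only, but the stated figures become less favourable. Raising the enrolment ceiling to about 14,000–15,500 before dropout would also close the gap, but it would need resources and ethics approval.
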